## Abstract

**Background:**

Hospitalized smokers often quit smoking, voluntarily or involuntarily; most relapse soon after discharge. Extended follow-up counseling can help prevent relapse. However, it is difficult for hospitals to provide follow-up and smokers rarely leave the hospital with quitting aids (for example, nicotine patches). This study aims to test a practical model in which hospitals work with a state cessation quitline. Hospital staff briefly intervene with smokers at bedside and refer them to the quitline. Depending on assigned condition, smokers may receive nicotine patches at discharge or extended quitline telephone counseling post-discharge. This project establishes a practical model that lends itself to broader dissemination, while testing the effectiveness of the interventions in a rigorous randomized trial.

**Methods/design:**

This randomized clinical trial (N = 1,640) tests the effect of two interventions on long-term quit rates of hospitalized smokers in a 2 x 2 factorial design. The interventions are (1) nicotine patches (eight-week, step down program) dispensed at discharge and (2) proactive telephone counseling provided by the state quitline after discharge. Subjects are randomly assigned into: usual care, nicotine patches, telephone counseling, or both patches and counseling. It is hypothesized that patches and counseling have independent effects and their combined effect is greater than either alone. The primary outcome measure is thirty-day abstinence at six months; a secondary outcome is biochemically validated smoking status. Cost-effectiveness analysis is conducted to compare each intervention condition (patch alone, counseling alone, and combined interventions) against the usual care condition. Further, this study examines whether smokers’ medical diagnosis is a moderator of treatment effect. Generalized linear (binomial) mixed models will be used to study the effect of treatment on abstinence rates. Clustering is accounted for with hospital-specific random effects.

**Discussion:**

If this model is effective, quitlines across the U.S. could work with interested hospitals to set up similar systems. Hospital accreditation standards related to tobacco cessation performance measures require follow-up after discharge and provide additional incentive for hospitals to work with quitlines. The ubiquity of quitlines, combined with the consistency of quitline counseling delivery as centralized state operations, make this partnership attractive.

**Trial registration:**

Smoking cessation in hospitalized smokers NCT01289275. Date of registration February 1, 2011; date of first patient August 3, 2011.

## Background

Smokers are more likely than nonsmokers to be hospitalized. Most smokers in the U.S. actually do quit smoking when hospitalized, however, the majority of them return to smoking soon after their discharge from the hospital [1-3]. Patients who continue to smoke after hospitalization are more likely to be re-hospitalized compared to those who quit and maintain abstinence [4,5]. Thus, helping hospitalized smokers quit smoking and remain abstinent after discharge will save lives and reduce costs in health care [6-11].

Research has found that brief counseling provided to smokers while they are hospitalized has limited effect on prolonged abstinence [6]. A 2007 Cochrane Review on studies of hospitalized smokers suggests that interventions need to last at least one month post-discharge to have a statistically detectable effect. This suggests that more intense intervention is needed to reduce relapse after discharge from the hospital. Hospitals are not set up to provide this level of follow-up care [12,13]. Quitlines have a robust infrastructure to deliver counseling services by telephone and are well suited to provide follow-up care. Meta-analyses have shown that telephone counseling is an efficacious intervention for smoking cessation [14]. Currently, publicly funded quitlines exist in every US state, collectively serving > 500,000 smokers each year [15]. Telephone counseling is convenient and can be delivered proactively, which can keep the rate of counseling high. The high rate of delivery of counseling is a critical factor for testing the intervention effect.

The nicotine patch is a widely used quitting aid. A 2008 Cochrane Review shows that the nicotine patch is an effective treatment for smoking cessation with an odds ratio of 1.66 [16]. However, it appears that nicotine replacement therapy (NRT) has little effect with hospitalized smokers [6]. The causes for the lack of NRT effect in this context are poorly understood. Moreover, not all hospitalized smokers use nicotine patches during their hospital stay. And fewer still leave the hospital with them, which may contribute to a quick relapse after discharge.

Telephone counseling is widely available and quitlines are well equipped to provide extended follow-up care. Nicotine patches are widely used but not systematically and proactively delivered to hospitalized smokers. Hospitals and quitlines can work collaboratively to intervene with this vulnerable population to help hospitalized smokers stay quit after discharge.

The current study is based on pilot work conducted by our research team at the California Smokers’ Helpline (CSH) in partnership with a local hospital (Scripps Mercy, San Diego). Using a two-group design (usual care (UC) versus nicotine patches at discharge plus proactive quitline counseling), 126 subjects were recruited, randomized, and evaluated at two months. The intervention group was over three times more likely to be abstinent at follow-up than the usual care (*P* < 0.01). Equally important for the current study is that the pilot program tested all the experimental procedures and showed the feasibility of recruitment, intervention, and evaluation [17].

The model of a quitline-hospital partnership is important because the new hospital accreditation requirements (Joint Commission) related to tobacco cessation performance measures include follow-up with hospitalized patients to assess smoking status [18]. Since hospitals may find it difficult to comply with the follow-up component, they may be less likely to select tobacco cessation as one of their four performance measures. Hospital staff are already pressed for time and finding time and funding for follow-up would be problematic. If hospitals do select tobacco cessation as one of their measures, there is a strong incentive for hospitals to work with partners like quitlines to both assess smoking status and provide follow-up counseling. The potential impact of the quitline-hospital partnership is not simply about dividing the work load between hospitals and quitlines, but also about follow-up counseling being more likely to occur and nicotine patches being more likely to be used, which would result in better outcomes for patients.

The specific aims of this study are:

1. To demonstrate the effects of two interventions, dispensing nicotine patches at discharge and providing proactive telephone counseling after discharge, on abstinence rates of hospitalized smokers, using a 2 x 2 factorial design.

2. To compare the cost-effectiveness of three intervention conditions: patches alone, counseling alone, and the combined interventions, against the usual care condition.

3. To examine if a patient’s medical diagnosis (for example, cardiopulmonary) is a moderating factor for intervention effects such that patients with certain diagnoses benefit more from the interventions than patients with other diagnoses.

4. To establish a practical model of a hospital-quitline partnership that can be adopted by other state quitlines and hospitals.

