### Sample size

This study uses a factorial design and was powered by marginal means (that is, the mean of the counseling factor averaged across levels of the nicotine patch factor) rather than the interaction. Sample size estimates were conducted using R [21]. Based on pilot work conducted in one of the hospitals with 120 patients, we assume the abstinence rates at six months will be 7% in usual care, 14% in proactive quitline counseling, 14% in the group receiving patches at discharge, and 21% in the group receiving both proactive counseling and patches [17]. Simulating binomial data from the assumed distribution, fitting generalized linear (binomial) models to the resulting data, and applying Hochberg’s (1988) [22] set-up procedure to the results, indicates that 298 subjects per cell is sufficient to have 80% power to see both main effects with the family-wise error rate controlled at the 0.05 level (two-sided). Assuming a variance inflation of 10% due to clustering and average follow-up rates of 80%, we need 410 subjects per cell - or 1,640 total - to have the same power for the mixed-effects complete-case analysis of the primary outcome with composite Type 1 error rate ≤ 0.05 (two-sided).

Hospital records suggest that about 30% of admitted smokers have cardiovascular or pulmonary diseases. This means, about 492 of the 1,640 subjects will be in this group, which allows for analysis of the moderating effects of diagnosis on interventions.

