#### Secondary aims

Secondary aims include assessing the possible moderating effects of diagnosis and determining the cost-effectiveness of the interventions. We will examine if subjects’ diagnosis (cardiovascular-pulmonary versus other diagnosis) moderates the effects of the intervention.

Analysis of cost-effectiveness depends on establishing an analytic perspective. In this study, we assume the hospital and quitline have the goal of maximizing benefits for subjects. We analyze cost per quitter. We assume that general costs are distributed evenly across callers since smokers are randomized. Personnel costs vary by position (for example, students have lower salaries than RTs) so staff time uses salary and benefits based on the personnel completing the various tasks (mailing materials, completing baseline assessment, and so on). We examine smokers who quit and re-hospitalizations prevented to establish the cost-effectiveness ratios for each intervention, in addition to (relative) quit and abstinence rates. To assess cost-effectiveness from the patient perspective, we evaluate quality-adjusted life years (QALYs). Quality of life weights are based on the health literature and life expectancy or, when necessary, modeled from clinician judgment of potential disease courses [41].

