## Discussion

This effectiveness trial employs a 2 x 2 factorial design to tease out the effects of two cessation interventions for hospitalized smokers. The randomized design is used here because strong real-world evidence for the effectiveness of interventions with hospitalized smokers is still needed. A 2007 Cochrane Review on this topic has found that for counseling to be effective with hospitalized smokers it needs to extend to at least one month post-discharge [6]. Counseling of this length is common for efficacy trials, but it is rare in real-world operations; hospital staff cannot typically follow up patients this long for preventive care. Moreover, the Cochrane Review found that nicotine replacement therapy (NRT), which has been shown efficacious in many trials [16], has little effect with hospitalized smokers [6]. The causes for the lack of NRT effect in this context are poorly understood. For these reasons, we test the proposed interventions, which include both dispensing nicotine patches and providing proactive telephone counseling, in a randomized factorial design.

The innovation of the study is in its ability to address several key issues in the field, all in one design:

1. It will answer the question of whether giving nicotine patches to smokers at discharge will increase the long-term quit rate, compared to what is naturally happening already. Since some hospitals may not be ready to link with a quitline, the study design will provide information as to whether the option of providing nicotine patches is sufficient to generate a statistically meaningful difference.

2. It will answer the question of whether linking hospital staff counseling with quitline counseling can increase the quit rate. The study will also provide detailed operational information on how much effort the quitline and the hospital have to put in to execute a counseling program with hospitalized smokers.

3. It will find out if providing both patches and counseling will be better than either intervention alone for this population. Since the costs of providing patches and counseling are relative easy to calculate in this case, this will allow a comparison on cost-effectiveness of these different interventions.

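### The cost-effectiveness ratios are defined against usual care, so the stated analysis does not report what adding the second intervention costs per extra quitter

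*Protocol article*

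**What the plan says.** The comparator is stated twice in the protocol article. Specific aim 2 (Background) reads "To compare the cost-effectiveness of three intervention conditions: patches alone, counseling alone, and the combined interventions, against the usual care condition". The abstract (Methods/design) says the same: "Cost-effectiveness analysis is conducted to compare each intervention condition (patch alone, counseling alone, and combined interventions) against the usual care condition".

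The Analytic plan (Secondary aims) gives the unit, "We analyze cost per quitter". It adds that quitters and prevented re-hospitalizations will be used "to establish the cost-effectiveness ratios for each intervention, in addition to (relative) quit and abstinence rates", with QALYs for the patient perspective. It names no comparison of the combined condition with patches alone or counseling alone.

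Item 3 of the Discussion is broader. It says of the trial: "It will find out if providing both patches and counseling will be better than either intervention alone for this population". It then says of the costs that "this will allow a comparison on cost-effectiveness of these different interventions". It gives no method for that comparison.

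No cost figures appear in the article. The planning abstinence rates (Sample size) are "7% in usual care, 14% in proactive quitline counseling, 14% in the group receiving patches at discharge, and 21% in the group receiving both" interventions.

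**The concern.** A hospital or quitline can adopt only one of the four conditions. The useful question is then what the next step up in cost buys. A ratio for the combination against usual care averages the first and second components, so it can look acceptable while the second component costs much more per extra quitter. A set of three such ratios also has no step that declares one option dominated by another.

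This bears on what the article sets out to do. Aim 4 is a model that other hospitals and quitlines can adopt. Item 1 of the Discussion notes that some hospitals may not be ready to link with a quitline, and asks whether patches alone are enough. For such a hospital the follow-on question is the added cost per quitter of counseling on top of patches. The stated ratios do not report that figure.

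**Working it through.** The article states no cost-effectiveness figure, so there is none to reproduce. The check asks how far the combined arm's ratio against usual care can lie from the incremental ratio.

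**Inputs.** Abstinence is 7% in usual care, 14% with either intervention alone and 21% with both (Sample size). Costs per subject, Cp for patches and Cc for counseling, are not given, so the cheaper component is set to 1 unit and the dearer to r units. Costs are assumed to add in the combined arm, and savings from avoided readmissions are ignored.

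**Formulas**, with p the combined abstinence rate:
- Both against usual care: (1 + r) / (p − 0.07)
- Both against the cheaper single intervention: r / (p − 0.14)

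**At the plan's rate, p = 0.21.** The denominators are 0.14 and 0.07, so the incremental ratio divided by the usual-care ratio is 2r / (1 + r).

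| r | Both vs usual care | Both vs cheaper single | Factor |
|---|---|---|---|
| 1 | 2/0.14 = 14.3 | 1/0.07 = 14.3 | 1.00 |
| 2 | 3/0.14 = 21.4 | 2/0.07 = 28.6 | 1.33 |
| 3 | 4/0.14 = 28.6 | 3/0.07 = 42.9 | 1.50 |
| 5 | 6/0.14 = 42.9 | 5/0.07 = 71.4 | 1.67 |

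Units are the cost of the cheaper component per extra quitter. The result is the same whichever component is dearer. Whenever r exceeds 1 at these rates, the dearer single intervention is dominated: it has the same 14% abstinence at higher cost. Its own ratio against usual care (r/0.07) is finite and does not say so.

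**Other combined rates (assumed, not in the article).**

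| p | r = 1 | r = 2 | r = 5 |
|---|---|---|---|
| 0.18 (less than additive) | 25.0/18.2 = 1.38 | 50.0/27.3 = 1.83 | 125.0/54.5 = 2.29 |
| 0.24 (more than additive) | 10.0/11.8 = 0.85 | 20.0/17.6 = 1.13 | 50.0/35.3 = 1.42 |

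In the cell below 1, the single intervention costs 1/0.07 = 14.3 per quitter and the step to both costs 10.0. The single intervention is then extendedly dominated, and usual care becomes the proper comparator for the combination. An incremental analysis finds this by itself.

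**A dominated combination.** The Background says nicotine replacement appears to have little effect in hospitalized smokers. Suppose, as an assumption, that patches add nothing: 7% in usual care and with patches alone, 14% with counseling alone and with both. With counseling at twice the cost of patches, the combination still shows 3/0.07 = 42.9 units per quitter against usual care. Counseling alone gives the same abstinence at 2 units instead of 3, so the combination is dominated.

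**Precision of the increment.** The planned 410 per cell gives 410 × 0.80 / 1.1 ≈ 298 effective subjects per cell. At two-sided 0.05, 14% against 21% has about 61% power. The same calculation gives about 80% for 7% against 14%, and over 99% for 7% against 21%.

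**The case against.** The strongest reply is that nothing in the article restricts the analysis to comparisons with usual care. The Discussion announces a comparison between interventions, and usual care may simply be the common reference. Ordering by cost, dominance rules and bootstrap intervals are details that a condensed article leaves to a fuller plan. This stands in part: the absence of those details is no fault. But the comparator is stated, in the aim and in the abstract, and the section describing the analysis does not extend it. The point concerns that stated choice and its mismatch with the Discussion.

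Second, a reader might infer that the trial cannot show whether the second intervention is worth its cost. The documents do not support that. With a common reference, every pairwise increment follows by subtraction from arm-level costs and quit rates, and the Secondary aims section reports quit rates as well. The gap lies in what is to be reported.

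Third, a reader might infer that the plan flatters the combined arm. That is not established either. At the planning rates there is no difference if the components cost the same, the direction can reverse with more-than-additive effects, and the article gives no costs.

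Finally, usual care is a legitimate comparator: it is current practice, and for a hospital weighing patches alone it is the right one. This supports keeping those ratios. It does not make them sufficient for choosing among four options.

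**Conclusion.** The point holds in a limited form. The stated cost-effectiveness comparison is each condition against usual care. It does not report the cost per extra quitter of adding the second intervention or flag dominated options, although the Discussion promises a comparison that needs both.

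The combined arm's ratio can understate the incremental cost. At the plan's rates the factor is 1.00 with equal component costs, 1.33 at 2:1 and 1.67 at 5:1, and it stays below 2 at any cost ratio. It reaches 2.29 at 5:1 if the combined rate is 18%, and falls to 0.85 at equal costs if that rate is 24%. The cost ratios and the 18% and 24% rates are assumptions, so the actual size is unknown.

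This is a secondary aim. The design, sample size, data collection and primary inference are unaffected.

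**What to change.** Amend specific aim 2, the matching sentence of the abstract and the Secondary aims section. Order the four conditions by mean cost, and remove dominated and extendedly dominated options. Report the incremental cost per additional quitter, per readmission avoided and per QALY against the next-best non-dominated option, with bootstrap intervals. Keep the ratios against usual care as descriptive results.

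The change needs no new data and no design change: it is another table from the same costs and outcomes. Its price is precision. With about 61% power for 14% against 21%, the abstinence difference behind the main increment would fail to reach significance about 39% of the time even if the planning rates are true, and its ratio will then be unstable. The intervals should show this, with the cost and effect differences given beside each ratio.

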## Methods

### Design

This study uses a 2 x 2 (patch by counseling) factorial design. Hospitalized patients are recruited from two health-care systems in San Diego County. Subjects provide signed informed consent and are randomly assigned by the computer to one of four conditions: usual care, proactive quitline counseling, nicotine patches at discharge, or both, in a 2 x 2 factorial design with an equal number of subjects per cell. Randomization is stratified by hospital and cigarettes per day (six to ten or eleven plus) and uses blocks of eight to keep a balance of characteristics across the four conditions. Smoking status is evaluated at baseline, two and six months after discharge. Cotinine-validated smoking status is assessed on all subjects who report abstinence and a random sample (25%) of subjects who report continued smoking at six months.

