### Setting

This study is conducted through two health-care systems, University of California, San Diego (UCSD) and Scripps, with a total of five hospitals. These hospitals have a combined licensed capacity of over 1,400 beds (Scripps has 873 and UCSD has 531) and are responsible for over 65,000 inpatient admissions each year. Estimates for smoking prevalence among these inpatients are 15 to 20%, providing a large pool from which to recruit. San Diego has a diverse population, including a large Latino population, which is reflected in the hospital population. Quitline counseling is provided by the California Smokers’ Helpline (CSH), the state quitline that is centrally operated from San Diego.

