**Figure 1 F1:**
[figure not shown]
**Flow diagram of the CHART Trial at UCSD and Scripps Hospitals.** Eligible patients are stratified by hospital and cigarettes per day and randomized into one of four groups in a 2 x 2 factorial design.

In the Scripps hospitals, respiratory therapists (RT) are responsible for recruitment of subjects and for nicotine patch delivery at discharge. They are also responsible for contacting the physician to obtain approval for study participation. Although the medical record is flagged for patients who are randomly assigned to receive nicotine patches, the electronic medical record system is not used for communication between the RT and the physician or pharmacy.

At the UCSD hospitals, subjects are recruited into the study by research staff (aka research recruiter or RR) provided by the CSH research team. The electronic medical record (EMR) is used extensively to communicate between research and hospital staff with many of the processes automated. A daily list of recently admitted smokers is generated from the EMR and is viewable by RRs. The physician approval process is also embedded in the EMR system. In this hospital system, smokers are approved for participation in the study unless physicians indicate in the EMR that they should not participate.

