#### Randomization

For this study, the CSH research team established and hosts a secure website that is used to randomize subjects into condition. The website complies with all HIPAA security guidelines for electronic protected health information (EPHI) [24]. All communication between hospitals and the California Smokers’ Helpline (CSH) is encrypted; identifying fields that are stored locally remain encrypted to ensure subject confidentiality. Staff responsible for recruitment and randomization enter the website through a password-protected web portal.

Recruitment staff (that is, RT and RR) complete the eligibility assessment and baseline measures, obtain signed informed consent from the smoker and approval from the physician. To complete the randomization procedure, staff use a web portal developed in-house to access the secure proprietary website. They enter the name, address, medical record number, phone number, cigarettes per day, and the anticipated discharge date of the smoker. The computer checks the name against a list of previously randomized subjects. If smokers are already in the study, a pop-up indicates their treatment condition and prevents re-randomization. If the smoker is not already in the study, the RT or RR confirms that the smoker is eligible, has provided signed informed consent, and that the physician has provided approval for study participation. The computer then randomly assigns the subject to condition. The condition is displayed to the RT or RR and all information is transmitted to CSH daily.

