## Trial status

This study has been approved by the relevant IRBs and recruitment is ongoing.

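### A single published block size of eight lets unmasked recruiters predict some upcoming allocations, a concealment weakness that is bounded and cheap to reduce

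*Protocol article*

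**What the plan says.** Under Design, the protocol article assigns subjects to four conditions "in a 2 x 2 factorial design with an equal number of subjects per cell". Randomization is stratified by hospital and by two levels of cigarettes per day, and it "uses blocks of eight to keep a balance of characteristics across the four conditions". No other block size is mentioned. Setting describes two health-care systems "with a total of five hospitals".

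Under Randomization, recruitment staff (respiratory therapists, RT, or research recruiters, RR) complete the eligibility assessment and baseline measures and obtain consent and physician approval. They then confirm these on a central website, and the computer assigns the subject. After that, "The condition is displayed to the RT or RR". If the patient entered has already been randomized, a pop-up shows the existing condition.

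Patch status can also be seen by other routes. In the Scripps hospitals, "respiratory therapists (RT) are responsible for recruitment of subjects and for nicotine patch delivery at discharge" (Recruitment process), and the medical records of patch subjects are flagged. At the UCSD hospitals, research staff can query the list of subjects assigned to patches (Nicotine patches).

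Trial status says that "recruitment is ongoing", so the block size became public during enrolment.

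**The concern.** With four equal conditions, every block of eight holds exactly two of each, or four patch and four no patch. Anyone who knows the block length and keeps a tally within a stratum can tell what remains in the block. The last allocation is then always known, and some before it are known or easier to guess.

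This matters because the people who could keep the tally also help decide who enters. Under Eligibility criteria, some conditions involve judgement: interest in staying quit, and an anticipated stay of at least 24 hours. Confidence to stay quit, a plausible predictor of the outcome, is asked at baseline, before assignment. The pool is also large. Setting gives over 65,000 admissions a year and 15% to 20% smoking prevalence, which is 9,750 to 13,000 smokers a year before eligibility is applied, against 1,640 needed. There is room to approach one patient now and another later.

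If the choice or timing of approach depended on the expected allocation, the arms could differ in motivation at entry. Both primary main effects would then be biased. The primary outcome is self-reported abstinence, for which motivation is an obvious confounder.

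**Working it through.** The article gives no figure for predictability, so there is none to reproduce. The calculation below is exact for a fixed block and simulated for partial views and varied blocks.

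**Inputs.** Block size 8, four conditions with equal allocation, two cigarette strata per hospital (Design); five hospitals (Setting); "we need 410 subjects per cell - or 1,640 total" (Sample size). If each hospital is its own stratum, there are 5 × 2 = 10 strata, averaging 1,640 / 10 = 164 subjects, or 164 / 8 = 20.5 blocks.

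**Upper bound: block size known, every earlier assignment in the stratum seen.**

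*Four-way, certain.* The 8th allocation is always known. The 7th is known only if the last two are the same condition, which has probability 1/7. The share is (1 + 1/7) / 8 = 1/7 = 14.3%, or about 1,640 / 7 = 234 subjects.

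*Four-way, best guess.* The guesser names the condition with most places left. The success probabilities for positions 1 to 8 are 0.250, 0.286, 0.333, 0.400, 0.443, 0.476, 0.571 and 1. Their mean is 3.76 / 8 = 47.0%, against 25% by chance. At least one condition is already ruled out for 54.3% of allocations.

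*Patch versus no patch, certain.* There are C(8,4) = 70 arrangements. The number in which the last r places are all alike is 2 × C(8 − r, 4 − r): 70, 30, 10 and 2 for r = 1, 2, 3 and 4. The share is (70 + 30 + 10 + 2) / 70 / 8 = 1.6 / 8 = 20.0%.

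*Patch versus no patch, best guess.* The position probabilities are 0.500, 0.571, 0.571, 0.629, 0.629, 0.714, 0.714 and 1. Their mean is 5.33 / 8 = 66.6%, against 50%.

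**Partial view (four-way).** The article does not say what share of a stratum one recruiter sees, so this range is assumed. Each earlier assignment is seen with the stated probability, and the block boundary is taken as known.

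| Share seen | Certain | Best guess |
|---|---|---|
| 100% | 14.3% | 47% |
| 75% | 2.6% | 38% |
| 50% | 0.2% | 33% |
| 25% | about 0% | 29% |

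**Randomly varied blocks (four-way).** The guesser sees the whole stratum and knows the set of sizes but not their order.

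| Block sizes | Certain | Best guess |
|---|---|---|
| 8 only | 14.3% | 47% |
| 4, 8 | 7.5% | 48.5% |
| 4, 8, 12 | about 3.6% | about 46% |
| 8, 12, 16 | about 2.2% | about 43% |

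Varying the size removes most of the certainty but only part of the guessing advantage. Including blocks of four gives back most of that gain, because short blocks are easy to guess.

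**The case against.** The best defence is that the article describes sound central assignment. The computer releases a condition only after eligibility, baseline measures, consent and physician approval are complete, and re-randomization is blocked. The bedside visit works from a daily list of admitted smokers, so approach is not a free choice. Eight is twice the smallest possible block for four conditions, and fixed permuted blocks are a recognised method. A condensed article may also leave further concealment steps to the full protocol.

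Much of this stands. It does not remove the point: central release protects the allocation being made, not the next one from a tally of those already made.

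A reader might infer more than the document supports:

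- *That recruiters see every assignment.* Each condition is displayed to the person making that randomization. Quality assurance refers to training for all RTs and recruitment staff, so there are several. Nothing says that any one of them sees a whole stratum or is told the block size at the site. The wider routes (flagged records, the patch list) reveal the patch factor only, and the pop-up shows only the condition of the patient entered.
- *That allocations can in general be worked out.* Even with a full view, about six in seven four-way allocations are not certain.
- *That the effect would be inflated.* This assumes that motivated patients are steered to active arms. Steering heavier or needier smokers to patches would bias the other way.
- *That no analysis could help.* Baseline measures include confidence to stay quit, days smoked and cigarettes per day, so imbalance can be examined and partly adjusted for.

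**Conclusion.** The concern holds as a vulnerability to selection bias. A single block size, stated publicly during enrolment, is combined with recruiters for whom no masking is described and who see the conditions they assign. The 14.3% certain and 47% best-guess figures (20% and 67% for patch versus no patch) are ceilings. They require knowledge of the block size and a full view of the stratum, which the document attributes to no individual. At an assumed 50% to 75% view, four-way certainty nearly disappears (0.2% to 2.6%), while guessing stays somewhat better than chance (33% to 38% against 25%).

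The direction of any bias is unknown. Baseline adjustment could correct it only in part, since motivation is incompletely measured. Nothing in the document shows that anyone predicted or steered an allocation. The point merits action because the change is easy while enrolment continues, not because the results are shown to be compromised.

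**What to change.** For all blocks not yet opened, have the randomization website draw the block size at random from larger multiples of four, such as 8, 12 and 16, separately within each hospital by cigarettes stratum. Amend the Design text of the protocol to say that block sizes vary, and keep the sizes out of site-facing and public documents until enrolment ends. Blocks already opened cannot be changed, and the use of eight is already known, so the benefit applies only from here on.

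The expected gain against a recruiter with a full view is a fall in certain four-way allocations from 14.3% to about 2.2%, and in best-guess success from 47% to about 43%. The residual guessing advantage should be acknowledged.

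The cost is a small change to randomization software developed in-house and a short amendment. An unfinished block of 16 can leave two conditions up to four apart within a stratum, against two for a block of eight. That is minor at about 164 subjects per stratum on average.
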